## 1 BACKGROUND

The low mechanical loading of bones among wheelchair users leads to an increased risk of bone fractures and associated complications due to low bone mineral density (BMD). Adding mechanical loading through physical activity in combination with optimizing nutrition may counteract these negative consequences in wheelchair users and thereby provide positive impact for bone health, as well as for physical and mental health. While there is a knowledge gap considering how to optimize bone health in wheelchair users, existing evidence allow us to hypothesize that the combination of bone-specific loading exercises and optimizing nutrition will be particularly effective for prevention and treatment of low BMD. Secondary, we expect positive effects on the participants physical and mental health in general.

In this project, a bone-specific exercise and nutrition program will be tailored to increase BMD in sport active and non-active wheelchair users with initial low-normal to low BMD. Using a randomized controlled design, participants will undergo a 24-week exercise and nutrition program, where main outcomes are change in BMD, blood bone markers, physical health, and mental health parameters. Based on the outcomes of the RCT, we will develop evidence-based practical health promoting recommendations and an implementation plan for health practitioners working with wheelchair users in the municipalities.

There are about 50.000 wheelchair users in Norway (according to NAV). Most research on bone health in wheelchair users has been performed on individuals with spinal cord injury (SCI). The incidence rate of osteoporotic fractures (related to low BMD) in SCI patients is as high as 2-3 fractures for every 100 patient-years (Zleik et al., 2019). Throughout life, 25 % of individuals with SCI experience at least one fracture, whereof 70 % of those fractures occur due to a low-impact injury such as moving from wheelchair to bed (Gifre et al., 2014). Furthermore, the Nordic population are genetically predisposed of low BMD, and it is estimated that up to 300.000 Norwegians suffer from osteoporosis (Folkehelseinstituttet, 2016). Therefore, there is reason to believe that the risk of fractures is even higher in Norwegian wheelchair users compared with the international numbers. In men with SCI, it has been shown that each unit of standard deviation (t-value) decrement in BMD at the femoral neck (hip) increases the risk of fracture by 280 % (Lazo et al., 2001). With the risk of fracture and fracture episodes rising exponentially every year after injury, this is an issue which deserves vast attention (Zehnder et al., 2004). Both BMD of the hip (non-functional body part) and the spine (functional body part) appear low in individuals with SCI (Smith et al., 2009, Kaya et al., 2006). Low BMD of the spine mainly involves increased risk of compression fractures (Lu et al., 2012), while low BMD of the hip and femur neck increases the risk of hip and femur fractures (Li et al., 2016).

Next to a high fractures rate, as much as 50 % of the fractures in individuals with SCI result in secondary complications (Abdelrahman et al., 2021). These complications include infections, pressure ulcers, autonomic dysreflexia, increased muscle spasticity, depression, ossification at the fracture site, stiffness, and a further decrease in bone health (Abdelrahman 2021 et al., Sugi et al., 2012). In addition to the massive impact on individual health and quality of life (QOL), these complications are of high socioeconomical impact due to an increased period of rehabilitation, additional treatments and, in some cases, prolonged periods of hospitalizations (>3 months) (Cochran & Smith, 1988). While there are no data on wheelchair users, Norwegians in general experience yearly 9.000 hip fractures, 15.000 wrist fractures and many compression fractures in the spine (Folkehelseinstituttet, 2016). The healing process of fractures is delayed in individuals with nerve damage, due to hormonal changes and reduced sympathetic function. These physiological changes create an unfavourable environment for bone formation and healing in the whole body and

not only in the non-functional areas (Schulte et al., 2017). As such, we can expect that the relative numbers of fractures and duration of recovery process is higher in wheelchair users. Consequently, prevention will be of strong value.

Physical activity is of great importance for bone health of wheelchair users with low mechanical bone load (Dolbow et al., 2011). Furthermore, physical activity benefits physical health, affecting factors such as cardiovascular and muscular fitness, body composition and obesity. Participation in sport is a major positive contributor to mental health, influencing wellbeing and QOL (Martin, 2013). In Norway, only 1-2 % of people with a physical disability are registered as active in a sport federation, compared with 36 % in the general population (NIF, 2019). Following the primary intervention to improve bone health, this project can also achieve secondary positive effects on both physical and mental health. With improved bone health, wheelchair users can be more physical active, avoid injuries and improve daily life functioning.

## 2 OBJECTIVES

The primary aim of this project is to investigate the effects of combined exercise training with high mechanical loading of bones and nutritional counselling for improving bone health in wheelchair users with an initially low-normal to low BMD (Z-score  $\leq 0.0$ ). Specifically, the following objectives are to determine the effects of the intervention on:

1. Bone health, measured as changes in BMD and blood bone markers.
2. Physical health, including body composition and muscular fitness.
3. Mental health, with focus on well-being, QOL and user experience.

Our secondary aim is to use this knowledge to develop recommendations and implementation plans for exercise and nutrition to promote bone health of wheelchair users.

This is the first study worldwide to implement a long-term bone-specific exercise and nutrition program focussing on improving bone health in wheelchair users. Furthermore, including a target group of both sport active and non-active participants allows us to dig deeper into the effect of the bone-specific exercise and not only of physical activity in general. Research in this group has been underprioritized, and this project will add valuable scientific and practical information on the effects of targeted exercise and nutrition for bone health, as well as the coinciding influence on general physical and mental health of wheelchair users.

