## 3 STUDY DESIGN

This multi-site study is a 24-week exercise intervention in which the participants also will receive nutritional optimization for bone remodelling. In this randomized controlled trial, interested participants will attend the lab at NIH, Western Norway University of Applied Sciences (HVL) or Norwegian University of Science and Technology (NTNU) for screening prior to being included and invited back for baseline testing. Subsequent randomization for the intervention or control group will be performed (see 4.5 Randomization). Supervised training in the initial four weeks of the intervention will be conducted on-site (NIH, HVL, NTNU), followed by monthly on-site sessions and off-site follow up with the intervention group. Nutritional optimization for bone remodelling will be provided to both groups. Repeated testing at the intervention midpoint and end of intervention aims to investigate the effect of the intervention.

[figure not shown]

**Figure 2: Schematic overview of the BoneWheel study.** Screening based on participant criteria will include eligible participants to progress to baseline testing and further to the randomized controlled trial. Images represents the test battery; Dual-energy X-ray Absorptiometry, questionnaires, physical tests (strength, rate of force development, function), blood sample, 24h dietary recall.

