## 6.2 Nutrition

All participants will receive and be asked to consume a mixed powder supplement (FrieslandCampina, the Netherlands) that consists of vitamin D (800 IU), calcium (250 mg) and whey protein (30 g) per dose, on three days of the week throughout the 24-week study period, to ensure stable intakes of key nutrients for optimized bone remodelling conditions. The supplement can be mixed in water or milk as per preference.

In the two weeks around the baseline, on three different days (two weekdays and one weekend day), 24h dietary recalls will be carried out by a trained nutritionist by audio- or videocall with each participant. This will be repeated around the test days in week 12 and week 24. One dietary recall will take 30-45 minutes and is structured in several steps to ensure the participant recalls as much as possible.

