## 6.3 Exercise intervention

The exercise intervention involves: 4 weeks of 3 sessions per week with supervised resistance training. Each session takes approximately 30 minutes. The training is carried out on-site (NIH, HVL or NTNU). From week 5, the participants train the 3 weekly sessions on their own in a suitable training site, with continued training at the study site one session every month throughout the rest of the intervention. During the entire period (24 weeks) the participants in the intervention group will complete 15 sessions at the study site and 57 sessions on their own.

The control group will not receive the exercise intervention and be asked to continue with their normal daily activities.

All participants will log their training and or physical activity, including the exercise intervention sessions for the intervention group (see attachment D3).

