## 6.5 Follow up

The intervention group will be contacted biweekly per telephone after the initial on-site training period for a short follow up conversation about how their exercise intervention is going.

All participants will receive feedback and counselling based on the dietary recalls and blood sample values after each test period. They will subsequently be administered commercially available supplements as per need if values are below Norwegian clinical reference values and or IOC guidelines for sport nutrition. Doses administered will be determined on individual basis by registered dietician and project lead [name] candidate and nutritionist [name] and or medical advisor [name].

Project partners medical advisor [name] (MD), physiotherapist [name] (PhD(c)) or Associate [name] (responsible for the mental health aspect of the study), will be sought to discuss any issues the participants may experience during the intervention and participants may be excluded from further participation and referred to their GP/the Norwegian Health care system for follow up in the case of discovery of serious medical issues.

After the study period, the participants will receive their last feedback and counselling session, as per, and within 6 months receive personal information about their bone health and physical progression in physical tests (muscular strength, rate of force development, function).

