## 10 TRIAL SPONSORSHIP AND FINANCING

NIH serves as the study sponsor, and the study is funded by the Dam Foundation. The funds are assigned to [name] (PI). The standard supplement used in both groups in the intervention, is produced and delivered by FrieslandCampina (the Netherlands) without commercial interest.

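### The primary aim and hypothesis concern combined exercise and nutrition, but both arms receive the nutrition, so the trial can only estimate the exercise programme added to nutrition

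*Protocol*

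**What the plan says.** **Aim and hypothesis.** Section 2 states the primary aim as to "investigate the effects of combined exercise training with high mechanical loading of bones and nutritional counselling for improving bone health in wheelchair users". Section 1 hypothesizes that "the combination of bone-specific loading exercises and optimizing nutrition will be particularly effective for prevention and treatment of low BMD" and describes what is tested as a 24-week programme of exercise and nutrition. The secondary aim in section 2 is to turn the findings into recommendations and implementation plans for both exercise and nutrition. Section 1 says that these will be based on the outcomes of the randomized trial.

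**What each arm receives.** Section 3 says of the design: "Nutritional optimization for bone remodelling will be provided to both groups". The detail agrees with this throughout:

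- Section 6.2, on the vitamin D, calcium and whey powder: "All participants will receive and be asked to consume a mixed powder supplement".
- Section 6.5 (Follow up), on dietary advice: "All participants will receive feedback and counselling based on the dietary recalls and blood sample values after each test period".
- The same section, on individual supplementation of those participants: "They will subsequently be administered commercially available supplements as per need".
- Section 10, on the powder: "The standard supplement used in both groups in the intervention".

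Section 6.3 says what is withheld: "The control group will not receive the exercise intervention and be asked to continue with their normal daily activities". Sections 3 and 6.5 (Follow up) add that the intervention group alone has on-site supervised sessions and biweekly telephone contact.

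**Comparison.** Section 4.5 defines two groups, allocated 1:1. Section 7.1 compares them in a mixed model with time, treatment and their interaction.

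**The concern.** The effect named in the aim is not the effect that the randomization isolates. Sections 1 and 2 treat the intervention as exercise together with nutrition. In sections 3 and 6, only the exercise part distinguishes the arms.

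This bears on what the trial may conclude. A positive difference could be presented as evidence for a combined programme that was never compared with its absence. A null difference could be taken to mean that the combination fails, although it would be equally compatible with nutrition having helped both arms and exercise having added little. The planned recommendations for practitioners would also cover nutrition, on which the randomized comparison is silent.

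This is not a matter left to a statistical analysis plan. The limit comes from which arms exist, and no model can recover a contrast that was not randomized.

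**Working it through.** The plan gives no figure to reproduce on this point. The check sets the components against the arms and asks which effects the two arms identify.

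**Step 1: components by arm**

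| Component | Intervention | Control | Protocol section |
|---|---|---|---|
| Powder supplement, 24 weeks | yes | yes | 6.2, 10 |
| Dietary feedback and counselling | yes | yes | 6.5 (Follow up) |
| Individual supplements as needed | yes | yes | 6.5 (Follow up) |
| Resistance exercise, 3 sessions a week | yes | no | 6.3 |
| Supervised on-site sessions (15 of 15 + 57 = 72) | yes | no | 6.3 |
| Biweekly telephone calls | yes | no | 6.5 (Follow up) |

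**Step 2: effects.** Let Y(e, n) be the mean change in spine BMD, the primary outcome in section 4.1. Here e = 1 means the exercise programme with its contact is given, and n = 1 means nutrition is given. Write E for the effect of exercise without nutrition, N for the effect of nutrition without exercise, and I for their interaction (synergy).

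- Randomized contrast: Y(1,1) − Y(0,1) = E + I. This is the effect of the exercise programme in people who receive nutrition.
- Combined effect: Y(1,1) − Y(0,0) = E + N + I.
- Nutrition effect: Y(0,1) − Y(0,0) = N.
- Synergy: Y(1,1) − Y(0,1) − Y(1,0) + Y(0,0) = I.

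**Step 3: what is observed.** The trial observes Y(1,1) and Y(0,1) only. The first line needs just these two. The combined and nutrition effects also need Y(0,0). Synergy needs both Y(0,0) and Y(1,0). Three of the four quantities are therefore not identified, including the one named in the aim.

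**Step 4: could change from baseline stand in for the missing arm?** No. Change within an arm mixes any treatment effect with the natural course over 24 weeks, and with regression to the mean, since participants are selected on a BMD Z-score at or below 0 (section 4.2). Without a nutrition-free control these cannot be separated.

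**Step 5: what e = 1 contains.** Exercise, supervision and calls differ together between the arms. The contrast therefore belongs to the exercise programme including its contact, not to mechanical loading alone.

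**The case against.** The strongest defence is that the design is sound and disclosed. Section 3 introduces the study as an exercise intervention in which participants also receive nutritional optimization, and says plainly that both groups get it. Section 6.2 gives a reason for supplementing everyone: stable intake of key nutrients. Matching the arms on nutrition is a proper way to isolate exercise, and a reader of sections 3 and 6 can work out the comparison. Section 2 also expresses interest in bone-specific exercise in its own right.

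Most of this stands. There is no hidden confounding by nutrition and no reason to alter the arms. Nor does any section plan to read change in controls as a nutrition effect, and how results would be reported is a risk, not something the protocol states. What the defence does not do is bring sections 1 and 2 into line. The remark on bone-specific exercise contrasts it with general physical activity, not with nutrition. A hypothesis that the combination is especially effective, and recommendations covering nutrition, go beyond reading the aim as exercise on a nutrition background.

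A reader might also infer that the trial is undersized because its controls are actively treated. The protocol does not support that. Section 4.1 describes its input as a difference between intervention and control group, drawn from an exercise study with a 3.5 % increase in spine BMD. That is the kind of contrast randomized here. If nutrition adds g percentage points in both arms, the difference is (3.5 + g) − g = 3.5, and no power is lost. A loss would require that the 3.5 % already contains a nutrition effect, or that nutrition adds less when exercise is present. The protocol states neither.

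**Conclusion.** The concern holds as a mismatch between the stated aim and hypothesis and the randomized contrast. The trial can estimate the effect of the exercise programme, with its supervision and calls, added to nutritional optimization. It cannot estimate the combined effect, the nutrition effect or synergy.

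The severity is moderate. The design is valid, and the randomization, outcome, sample size and model are unaffected. What changes is the claim that the result can carry. The conclusion rests only on the protocol's allocation of components to arms, on which sections 3, 6.2, 6.5 (Follow up) and 10 agree. It needs no numerical assumption.

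**What to change.** 1. In section 2, restate the primary aim along these lines: *to determine the effect of a 24-week bone-specific exercise programme, including its supervision and follow-up contact, added to nutritional optimization, compared with nutritional optimization alone*. Keep the population and outcomes as they are.
2. In section 1, reword the hypothesis to the same contrast, and use the term intervention consistently with sections 3 and 6.3.
3. With the secondary aim in section 2 and the matching text in section 1, state that the randomized comparison supports conclusions about exercise on a nutrition background only, and that any nutrition recommendations rest on other evidence.

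Section 4.1 needs no change on this account. The cost is a few sentences and a narrower claim. Claiming the combined effect would instead need an arm with neither component, and claiming synergy would need a full factorial design. Neither is necessary for the question that the present design answers.

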## 3 STUDY DESIGN

This multi-site study is a 24-week exercise intervention in which the participants also will receive nutritional optimization for bone remodelling. In this randomized controlled trial, interested participants will attend the lab at NIH, Western Norway University of Applied Sciences (HVL) or Norwegian University of Science and Technology (NTNU) for screening prior to being included and invited back for baseline testing. Subsequent randomization for the intervention or control group will be performed (see 4.5 Randomization). Supervised training in the initial four weeks of the intervention will be conducted on-site (NIH, HVL, NTNU), followed by monthly on-site sessions and off-site follow up with the intervention group. Nutritional optimization for bone remodelling will be provided to both groups. Repeated testing at the intervention midpoint and end of intervention aims to investigate the effect of the intervention.

[figure not shown]

**Figure 2: Schematic overview of the BoneWheel study.** Screening based on participant criteria will include eligible participants to progress to baseline testing and further to the randomized controlled trial. Images represents the test battery; Dual-energy X-ray Absorptiometry, questionnaires, physical tests (strength, rate of force development, function), blood sample, 24h dietary recall.

## 4 PARTICIPANTS

### 4.1 Number of participants

Power calculation is performed using GPower 3.1. The primary outcome and focus of the RCT is change in BMD of the spine. Mean and standard deviations for a relevant difference between intervention and control group is based on a previous 24-week exercise intervention that showed a significant increase in BMD of the spine of 3.5 % (Rubin et al., 2020). Based on an 80 % power at a significance of  $P=0.05$ , the sample size needed to detect a relevant change in BMD of the spine would be 22 persons in each group. To account for a potential 35 % dropout rate, **30 participants** will be included in each group. Based on ~39% prevalence of BMD Z-score of the spine  $\leq 0$  SD in the wheelchair users in the ParaNut study (unpublished), we assume ~150 participants need to be screened. However, in order to reach this number of participants, we include wheelchair users with BMD Z-score  $<0$  at any measured site. We believe that a participant with Z-score  $>0$  at lumbar spine also could benefit from the intervention. Furthermore, as Z-scores of the hip and femur neck are secondary outcome parameters, we choose to include participants with a Z-score  $<0$  at any measured site.

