#### 4.5 Randomization

Based on physical activity level, each participant will be categorized as non-active, moderately active, and very active (see 5.6 Questionnaires). Eligible participants will be randomly assigned to one of the two study groups, an intervention group (n=30) or a control group (n=30). The randomization list will be created using Randomizer.org, and stratified by physical activity status, sex, and SCI/non-SCI, with a 1:1 allocation using random block sizes of 4, 6, and 8. To ensure allocation concealment, we will use sequentially numbered, non-transparent envelopes containing the treatment allocation information. The groups will be checked for distribution of age, medication use, degree of injury/disability, and degree of wheelchair use.

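### Losing 35% of 30 per group leaves 19.5, not the 22 per group that protocol section 4.1 requires for 80% power

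*Protocol*

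**What the plan says.** Protocol section 4.1 names change in spine BMD as the primary outcome and sizes the trial on it. The calculation is "Based on an 80 % power at a significance of" 0.05, and its conclusion is that the number required "would be 22 persons in each group. To account for a potential 35 % dropout rate". The second of these sentences goes on to set enrolment at 30 per group.

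Section 4.5 uses the same target, with "an intervention group (n=30) or a control group (n=30"), so 30 is the operative figure and not a slip confined to one sentence. Allocation is 1:1.

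On the effect size, section 4.1 says "Mean and standard deviations for a relevant difference between intervention and control group is based on a previous 24-week exercise intervention", which found a "significant increase in BMD of the spine of 3.5" %. It prints no standard deviation, no standardized effect and no statement of whether the test is one- or two-sided.

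**The concern.** A dropout allowance should enrol enough people that the required number remains after the assumed loss. Section 4.1 gives all three quantities involved (22 needed, 35% lost, 30 enrolled), so the claim can be checked directly. It fails, because 30 less 35% is fewer than 22.

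At stake is the stated 80% power for the primary outcome. If dropout reaches the rate the protocol says it has provided for, the trial will have fewer completers than its own calculation requires. A reader of section 4.1 would also believe that the trial withstands more attrition than it does.

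**Working it through.** **Inputs.** Required number per group 22, power 80%, significance level 0.05, dropout 35% and enrolment 30 per group, all from section 4.1. Section 4.5 repeats the 30 and gives the 1:1 allocation. The 22 is taken as given: it cannot be re-derived, because no SD or standardized effect is printed.

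**1. Reproducing the 30.**
- Required number times (1 + dropout): 22 x 1.35 = 29.7, rounded up to 30. This matches the protocol.
- Required number divided by (1 - dropout): 22 / 0.65 = 33.85, rounded up to 34. This does not match.

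The match makes the first form the likely source. That is an inference, and the steps below do not depend on it.

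**2. What 30 per group leaves.**
- At 35% dropout: 30 x 0.65 = 19.5 per group, 39 in total, against 22 and 44 required.
- With 34 per group: 34 x 0.65 = 22.1, which is enough.
- Largest dropout at which 30 still leaves 22: 1 - 22/30 = 26.7%. At 26%, 30 x 0.74 = 22.2 remain. At 27%, 30 x 0.73 = 21.9 remain, just short.

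**3. Power at 35% dropout, counting completers only.** Assume a two-sided 5% two-sample comparison and solve for the standardized difference d at which 22 per group gives exactly 80% power. Then evaluate power at 19, 19.5 and 20 per group.

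Normal approximation: d = sqrt(2/22) x (1.960 + 0.842) = 0.845, and power at n per group is Phi(d x sqrt(n/2) - 1.960). At n = 19.5 this is Phi(0.845 x 3.122 - 1.960) = Phi(0.678) = 75.1%.

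The t-test with the noncentral t distribution gives d = 0.865 and nearly the same power:

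| Assumption (t-test) | 19 per group | 19.5 per group | 20 per group |
|---|---|---|---|
| Two-sided, 22 gives exactly 80% | 73.7% | 74.8% | about 76% |
| Two-sided, 22 rounded up from just above 21 | 75.7% | 76.9% | about 78% |
| One-sided, 22 gives exactly 80% | 74.5% | 75.5% | 76.5% |
| One-sided, 22 rounded up from just above 21 | 76.3% | 77.3% | 78.2% |

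The second and fourth rows are the most favourable rounding. Power stays below 80% in every case, within about 74% to 78%.

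**The case against.** The strongest counter-argument is the analysis model. Section 7.1 plans a linear mixed model that uses every available outcome, and section 6.4 repeats the DXA scan at week 12. Someone lost after week 12 therefore still contributes, and a completers-only power figure is conservative. That stands as a caution about the size of the loss. It does not justify the 30: section 4.1 takes 22 persons as the number needed, then adds a dropout allowance, with no credit claimed for partial data. How much would be recovered cannot be computed from the protocol. Section 7.1 also plans a per-protocol analysis, where partial data may help less.

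It can also be said that 35% is only a potential rate and the loss of power is modest. Both are fair, and they limit how serious the point is. But the 30 is presented as providing for that very rate, and it does not.

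Two stronger readings are tempting and not supported:
- A reader might infer that the protocol demonstrably used 22 x 1.35. No formula is printed, so this is a likely explanation and no more.
- A reader might turn the shortfall into a larger detectable BMD difference, or an implied SD, by treating 3.5% as the between-group difference. Section 4.1 describes 3.5% only as an increase seen in a previous intervention. It does not say that this is the difference between groups on which the 22 was computed.

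**Conclusion.** The point holds as an inconsistency among three printed figures. Thirty per group does not leave 22 after 35% dropout. It leaves 19.5, and 34 would be needed to keep both the 35% and the 80%. This conclusion needs no assumption beyond the protocol's own numbers.

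The effect on power does rest on assumptions: that 22 is correct, that only completers count, and that the comparison behaves like a two-sample test of means at 5%. On that basis power at 35% dropout is about 74-76% if 22 gives exactly 80% (two-sided about 74-76%, one-sided about 75-76%), and up to about 78% if 22 was rounded up. The loss is about 2 to 6 percentage points, possibly less once partial data enter the mixed model.

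This does not show that the trial is seriously underpowered. Enrolment still protects the required 22 per group up to 26.7% dropout. Whether 22 is the right base cannot be judged from the protocol.

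**What to change.** Restate section 4.1 so that its figures agree. Either of these does it without enrolling more people:

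- *Thirty per group (60 in total) retains the 22 per group needed for 80% power at up to about 26% dropout.*
- *With 35% dropout, 60 enrolled leave about 39 completers in total (19-20 per group), with power of roughly 74-78% instead of 80%, counting completers only.*

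The second wording should carry its assumptions (sidedness, and 22 taken as the base). The sponsor holds the effect size and SD behind the 22 and can replace the range with one figure. If partial data from the mixed model are meant to cover the gap, section 4.1 should say so and quantify it.

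The cost is one sentence and a less favourable statement of either the dropout tolerance or the power. Design, allocation, endpoint and analysis are unchanged.

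Keeping both 35% and 80% would instead need 34 per group (68 in total). The group sizes in section 4.5 would then change, and so would the screening estimate of about 150: at the stated prevalence of about 39%, 60 / 0.39 is about 154 and 68 / 0.39 about 174.
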